### EBT fidelity boost, part 1: train therapists to self-monitor by mimicking observational coding methods

One major step toward boosting the capacity of community therapists to implement EBTs with fidelity is improving their ability to accurately monitor (i.e., recognize and assess) the EBTs they are expected to deliver. There is consensus that training clinicians to self-report accurately on EBT delivery is a pragmatic strategy for tracking and ultimately improving EBT fidelity in usual care [19]. Self-report fidelity procedures are quick, inexpensive, non-intrusive, and compatible with electronic medical record systems, making them sustainable in everyday service contexts. They are also flexible in that they can capture fidelity to specific treatment manuals or to core treatment techniques associated with evidence-based approaches [21].

However, for fidelity self-monitoring to be useful, there remains a major psychometric hurdle to clear: Studies attempting to confirm the validity of therapist self-ratings of EBT fidelity by comparing them with observer ratings have mostly produced disappointing results, casting doubt on the accuracy with which therapists can judge their own performance. Research with both adult and youth populations has logged modest to weak concordance between therapist and observer reports of fidelity to various EBTs. And although a handful of studies (e.g., [21]) have found moderate *reliability* (i.e., adequate correlations) between therapists and observers when reporting on EBT utilization, these studies also found that therapists showed uniform *inaccuracy*: They reported much greater average use of EBTs (i.e., significantly higher mean fidelity scores) than did observers. Overall, weak concordance with trained observers is a universal therapist bias that affects research-trained clinicians delivering manualized EBTs as well as clinicians in usual care.

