**Fig. 1 Fig1:**
[figure not shown]
Training process schematic: Measurement Training and Feedback System for Implementation (MTFS-I) of FT and CBT techniques

This randomized trial will first collect data on existing delivery of FT and CBT techniques for youth with AEPs in four outpatient behavioral health sites (Baseline phase). It will then experimentally compare the boost in FT and CBT fidelity produced when clinicians are randomized to one of two study conditions (Implementation phase): Training Only versus Training + Feedback + Consultation. Study data will include (1) post-session therapist-reported checklists on EBT use and (2) audiotapes of treatment sessions that will be observationally coded by research staff. Study Aim 1 will compare Baseline versus Implementation phases in EBT self-monitoring and EBT utilization, combining across sites. We expect that both self-monitoring (reliability, accuracy) and technique use (FT, CBT) will be significantly greater during the Implementation phase, after initiation of MTFS-I training. Study Aim 2 will experimentally test the effects of one MTFS-I component (Training Only) versus a full MTFS-I package that includes both system components plus ongoing expert facilitation (Training + Feedback + Consultation). We expect that Training + Feedback + Consultation will be superior to Training Only in promoting EBT self-monitoring and technique use. We will also examine the strength of correlation between self-monitoring and technique use via within-subject (comparing study phases) and between-subject (comparing study conditions) analyses.

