### Data analysis plan

Study data will have a three-level nested structure: clients within therapists within sites (we will average across sessions for each client). The basic analytic approach for these nested data will be multilevel mixed effects models examining the effects of Phase (Baseline versus Implementation) and Condition (Training Only versus Training + Feedback + Consultation) on dependent variables aggregated across each time period: 4-month Baseline phase (prior to MTFS-I training) and 12-month Implementation phase. We will use maximum likelihood estimation for continuous variables and robust weighted least squares for categorical variables. We will model Site and Therapist as random effects in all models. We will include Therapist (age, sex, race/ethnicity, experience, EBT attitudes, EBT proficiency) and Client (age, sex, race/ethnicity) factors at their respective levels to examine potential effects. Effect sizes will be calculated using the standardized *d* effect size indicator, interpreted as the standardized difference between contrasts for Phase and Condition comparisons [41]. Aim 1 exploratory contrasts will examine the Phase (within-subjects) effect, contrasting Baseline versus Implementation across all sites in EBT self-monitoring (reliability, accuracy) and EBT technique use (averaging across FT and CBT techniques). Aim 2 will experimentally test the Condition (between-subjects) effect on MTFS-I uptake, EBT self-monitoring, and EBT technique use.

To analyze EBT self-monitoring, reliability between therapists and observers on FT and CBT technique use will be calculated using the ICC_2,2_ [44]. Conditions will be compared on the relative magnitude of ICCs for each EBT scale. To compare conditions on therapist accuracy, we will use statistical equivalence testing methods, applying the confidence interval approach [45] to examine whether therapist scores are equivalent to corresponding observer scores. To analyze EBT technique use, a series of multilevel mixed effects models will be conducted with a dummy-coded Condition variable included at the Therapist level to test the contrast of main interest; alpha will be adjusted to account for multiple contrasts. For the Aim 1 analyses of Phase contrasts, a product interaction terms will be included to examine Phase by Condition effects; for significant interactions, we will test simple effects by examining Phase contrasts separately within condition.

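### Aim 2 promises a test of self-monitoring, but therapist-observer reliability is only ranked between conditions, using an index, ICC(2,2), that describes an unused two-rater average and overlaps with accuracy

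*Protocol article*

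**What the plan says.** All of the following is in the protocol article.

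- **Index** (Data analysis plan): "reliability between therapists and observers on FT and CBT technique use will be calculated using the ICC_2,2".
- **Comparison rule** (next sentence): "Conditions will be compared on the relative magnitude of ICCs for each EBT scale". No test, interval, margin or alpha is attached to it.
- **Status of the outcome** (same section): "Aim 2 will experimentally test the Condition (between-subjects) effect on MTFS-I uptake, EBT self-monitoring, and EBT technique use". Under Protocol summary and specific aims, the direction is predicted: "We expect that Training + Feedback + Consultation will be superior to Training Only in promoting EBT self-monitoring and technique use".
- **The neighbouring outcomes** (same section): therapist accuracy is compared by equivalence testing with confidence intervals. Technique use is compared by multilevel models, and the alpha adjustment for multiple contrasts is stated in that sentence.
- **Reliability and accuracy as separate ideas** (Background, EBT fidelity boost, part 1): a handful of earlier studies "have found moderate *reliability* (i.e., adequate correlations) between therapists and observers when reporting on EBT utilization", while the therapists in them were inaccurate: "They reported much greater average use of EBTs (i.e., significantly higher mean fidelity scores) than did observers".
- **The score in use** (MTFS-I feedback component): feedback reports rest on the therapists' own checklist ratings.

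**The concern.** Two things do not fit together.

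First, the section promises a test of the Condition effect on self-monitoring, but for the reliability half of that outcome it gives a rule that yields only an ordering. A group-level ICC is one number per condition, so the general mixed-model sentence does not supply the missing inference.

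Second, ICC(2,2) answers a different question. In standard notation the first digit denotes the two-way random, absolute-agreement form, and the second denotes the mean of two ratings. The practical question is how well one therapist's report tracks the observer. An absolute-agreement index also responds to a mean shift between therapist and observer, which the plan already handles as accuracy. If the full package only reduces over-reporting, both outcomes would improve, and one effect could be read as two.

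At stake is whether a statement that the full package improves self-monitoring reliability has evidence behind it.

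**Working it through.** The article gives no value for an ICC or its precision, so there is no stated figure to reproduce on this point. The sample-size input does reproduce: 192 clients × 1.5 recordings = 288 coded recordings.

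**Inputs from the article:** two raters per pair; 288 coded recordings; a 4-month Baseline and a 12-month Implementation phase; therapists complete FT items, CBT items or both.

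**Assumptions, not in the article:** single-rating consistency c (0.50 unless stated); therapist mean shift D of 0 to 1 SD; recordings per condition of
- 144 (288/2, as if every coded recording fell in Implementation),
- 108 (288 × 12/16 / 2, even accrual over 16 months),
- 54 (half of 108 on one EBT scale).

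**Step 1, effect of averaging.** With no mean bias, ICC(2,2) = 2r/(1 + r), where r is the single-rating ICC.

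| r | ICC(2,2) |
|---|---|
| .30 | .46 |
| .40 | .57 |
| .50 | .67 |
| .60 | .75 |

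The function increases in r, so for given data it cannot reverse the order of two conditions relative to ICC(2,1).

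**Step 2, effect of a mean shift.** Set the within-rater variance to 1, split into c (true) and 1 − c (error). A shift D adds rater variance D²/2. Then ICC(2,2) = c / [c + (D²/2 + 1 − c)/2]. With c = .50:

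- D = 0: .50/(.50 + .25) = .67
- D = 0.5: .50/(.50 + .3125) = .62
- D = 0.8: .50/(.50 + .41) = .55
- D = 1.0: .50/(.50 + .50) = .50

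The consistency index ICC(3,1) stays at .50 throughout. ICC(2,2) equals ICC(3,1) when D²/2 = 1 − c, that is D = √(2(1 − c)), or 1.0 SD at c = .50. Beyond that shift ICC(2,2) is the lower of the two.

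**Step 3, what the overlap does to the comparison.** In 4,000 simulated trials with 108 recordings per condition and c = .50 in both:

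| Over-reporting in the two conditions | Mean ICC(2,2) difference | ICC(2,2) favours the less biased condition | ICC(3,1) favours it |
|---|---|---|---|
| 0.8 vs 0 SD | .12 | 89% | 50% |
| 0.8 vs 0.4 SD | .08 | 80% | 49% |

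**Step 4, ranking with no true difference.** Same simulation, c = .50 and no bias in either condition. The full package has the larger ICC in about 50% of trials on each scale. If the two scales were independent, it would lead on at least one in 1 − .5² = 75% and on both in 25%.

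| Recordings per condition | ICC(2,2) differs by more than .10 by chance | SD of the ICC(3,1) difference | 95% half-width (1.96 × SD) |
|---|---|---|---|
| 144 | 21% | .089 | .17 |
| 108 | 28% | .102 | .20 |
| 54 | 44% | .148 | .29 |

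These figures treat recordings as independent. Adding therapist-specific bias (30% of the therapist's error variance, 12 therapists per condition) barely changed the SD at 108 (.104). Clustering of technique use itself was not simulated.

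**The case against.** The best defence is that this is a condensed article: it does not exclude an interval or test, and resampling details are usually left to an analysis plan. That stands as to detail. It does not explain why a comparison rule is written down for reliability that falls short of the test promised in the same section, when accuracy and technique use each have an inferential method there.

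Several stronger readings are tempting and are not supported:

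- **That averaging could produce the between-condition result.** It cannot (Step 1). It changes only the level reported.
- **That reliability is always overstated.** This is so relative to ICC(2,1). Relative to ICC(3,1) the excess vanishes at a shift of about 1 SD when consistency is .50.
- **That the trial defines reliability as a correlation.** That wording describes earlier studies. The trial's operational definition is the ICC. Absolute agreement is also inferred from the notation; if a consistency form was meant, the overlap with accuracy falls away and the averaging point remains.
- **That the intervention will inflate the ICC by raising true variance.** The article predicts higher mean technique use, not higher variance, and any ICC, including ICC(3,1), shares that dependence.
- **That a confirmatory Aim 1 claim is at risk.** The Data analysis plan labels the Aim 1 contrasts exploratory.

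The separate accuracy analysis would also let a reader see a mean shift, so the overlap is a risk of double counting and not a certain error.

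**Conclusion.** The point holds in this limited form. As written, the reliability part of Aim 2 yields an ordering with no inference, although the same section promises a test. With equal true ICCs that ordering favours the full package about half the time per scale. ICC(2,2) values more than .10 apart arise by chance in 21% to 44% of trials over the assumed 144 to 54 recordings per condition.

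The index is also poorly matched to the question. It describes a therapist-observer mean that is not used, and it moves with the bias that is analysed as accuracy. The sizes depend on the assumed consistency, bias, recording counts and split over scales, none of which the article gives. The comparison is affected by the mean-shift overlap and the lack of inference, not by the averaging. This should be corrected, but it does not touch the technique-use analysis.

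**What to change.** - **Index.** Report the single-measure consistency ICC, ICC(3,1), on same-session therapist-observer pairs as reliability. Leave mean bias to the equivalence analysis.
- **Comparison.** For each EBT scale, estimate the difference in ICCs between conditions. Test it by permuting therapist assignment within site, as randomized. Add an interval from resampling therapists within arm, with a small-cluster correction.
- **What to avoid.** Do not resample within site-by-arm strata. With 6 active slots per site (8 with replacements), an even split gives 3 to 4 therapists per stratum. The factor (m − 1)/m then understates the standard error by 1 − √(2/3) = 18% to 1 − √(3/4) = 13%.
- **Multiplicity.** Place these comparisons under the alpha adjustment already stated for technique use.
- **Aim 1.** Use the same index descriptively for the exploratory phase contrast.
- **Optional.** Report the therapist-observer disagreement variance per arm, because any ICC depends on between-session variance.

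The cost is a few sentences in the plan and a short program, with no new data. The downside is that coefficients will usually look lower than ICC(2,2). The interval will also be wide: half-widths of about .17 to .29 under the assumptions above.

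### The method named for comparing conditions on therapist accuracy tests therapist against observer scores, not the between-condition difference that Aim 2 hypothesizes

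*Protocol article*

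**What the plan says.** All the relevant statements are in the protocol article.

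- **Hypothesis** (Protocol summary and specific aims): "We expect that Training + Feedback + Consultation will be superior to Training Only in promoting EBT self-monitoring and technique use". The same section defines self-monitoring as reliability and accuracy.
- **Aim 2 contrast** (Data analysis plan): "Aim 2 will experimentally test the Condition (between-subjects) effect on MTFS-I uptake, EBT self-monitoring, and EBT technique use".
- **General approach** (Data analysis plan): "multilevel mixed effects models examining the effects of Phase (Baseline versus Implementation) and Condition", applied to dependent variables that the sentence does not list.
- **Accuracy** (Data analysis plan): "To compare conditions on therapist accuracy, we will use statistical equivalence testing methods", using a confidence interval approach, "to examine whether therapist scores are equivalent to corresponding observer scores".
- **Technique use** (Data analysis plan): "To analyze EBT technique use, a series of multilevel mixed effects models will be conducted with a dummy-coded Condition variable". This is the only outcome for which a Condition term is written out.

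**The concern.** The accuracy sentence begins with one purpose, comparing conditions, and ends with a test of something else, agreement between therapist and observer means. An equivalence test of therapist against observer has the null that their means differ by at least a margin. Aim 2 needs the null that the two conditions have the same discrepancy. No combination of verdicts on the first null is a test of the second. If one condition meets equivalence and the other does not, that does not show the conditions differ. If both fail, nothing has been learned about which is closer to the observers.

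Accuracy is one of the two components of self-monitoring, which is one of the two therapist behaviors that MTFS-I is built to change. An analyst who followed the accuracy sentence literally could report a difference that is not there or miss one that is.

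**Working it through.** The plan gives no margin, error rate or power for the accuracy analysis, so there is no stated figure to reproduce. The only power statement, in the Power analysis section, concerns a between-condition effect and is a separate matter. The check asks how equivalence verdicts by condition behave when used as the comparison.

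**Inputs from the Power analysis section:** 32 therapists, 6 clients each, within-cluster ICC .05.

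**Assumptions (not in the article):** 16 therapists per condition; all 6 clients contribute in the Implementation phase; client-level discrepancy (therapist minus observer) with SD 1; equivalence declared when the 90% CI lies inside ±0.3, ±0.4 or ±0.5 SD; common bias from 0 to 0.3 SD when the arms are equal, and up to 1.2 SD when they differ; direct test two-sided at 5%.

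**Precision**

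- Variance of a therapist mean: .05 + .95/6 = 0.208.
- SE of one arm's mean discrepancy: √(0.208/16) = 0.114. With t(15) = 1.753, the 90% CI half-width is about 0.20.
- SE of the between-condition difference: √2 × 0.114 = 0.161.

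At a margin of 0.4, an arm therefore passes only if its observed mean discrepancy is within about 0.4 − 0.2 = 0.2 SD of zero. An arm whose true bias is 0.2 passes about half the time.

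**Equal accuracy in both arms.** If each arm passes with probability p, the verdicts disagree with probability 2p(1 − p), and they disagree in favor of the full package with probability p(1 − p). At p = .512 this gives 2 × .512 × .488 = 50% and 25%. Simulation, 20,000 runs per row:

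| Margin | Common bias | Each arm passes | Verdicts disagree | Only full package passes | Direct test significant |
|---|---|---|---|---|---|
| 0.3 | 0 | 61% | 47% | 24% | 4.9% |
| 0.3 | 0.3 | 5% | 10% | 5% | 4.9% |
| 0.4 | 0 | 91% | 16% | 8% | 4.9% |
| 0.4 | 0.2 | 51% | 50% | 25% | 4.9% |
| 0.5 | 0 | 99% | 2% | 1% | 4.9% |
| 0.5 | 0.3 | 51% | 50% | 25% | 4.9% |

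Over all twelve equal-arm scenarios, disagreement ran from 2% to 50%, or 1% to 25% in the hypothesized direction only. The like-for-like figure for the direct test in one direction is about half of 4.9%.

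**A real difference between arms** (Training Only bias versus full-package bias):

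| True biases | Difference | Only full package passes, margins 0.3 / 0.4 / 0.5 | Direct test significant |
|---|---|---|---|
| 0.5 vs 0.2 | 0.3 | 21% / 51% / 76% | 44% |
| 1.2 vs 0.9 | 0.3 | 0% / 0% / 0% | 44% |
| 1.2 vs 0.7 | 0.5 | 0% / 0% / 0% | 85% |

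The same 0.3 SD difference is signaled in anything from 0% to 76% of trials, depending on where the arms sit relative to the margin. In the last row, even the better arm at a margin of 0.5 would need an observed mean below 0.5 − 0.2 = 0.3, which is (0.7 − 0.3)/0.114 = 3.5 SE under its true value. Both arms fail in 100% of runs. The direct test has 0.5/0.161 = 3.1 SE to work with.

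**The case against.** **The general model covers it.** The plan says mixed models will examine Condition, that Aim 2 tests Condition on self-monitoring, and that effect sizes will be given for Condition comparisons. This stands in part. A reader might infer that accuracy has no randomized test at all, and the article does not support that: the intent is stated. What it lacks is a matching procedure. No therapist-minus-observer discrepancy is defined as a model outcome, and the sentence that does address accuracy names a test with another null. A fuller plan may add detail, but here a method has been named, and it does not answer the aim.

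**No pass/fail rule is stated.** Correct. A reader might infer that the trial will claim superiority when one arm passes and the other fails. The article does not say so; intervals could instead be compared informally across arms. Reading the tests by condition is the natural way to use them for comparing conditions, but it is an inference. A single pooled test would say still less about a condition difference.

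**The error rates depend on assumptions.** They do. A reader might take 50% as the false-positive rate. It is the top of an assumed range, it counts disagreement in both directions, and it falls toward zero when over-reporting is large, because both arms then fail. The Background says of therapists in earlier studies: "They reported much greater average use of EBTs (i.e., significantly higher mean fidelity scores) than did observers". That makes a missed real difference the likelier error here.

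**Cancellation.** A reader might add that over-raters and under-raters could cancel, so that an arm of poor self-raters passes. This carries little weight: the Background describes the inaccuracy as running uniformly in one direction and treats it as a difference in means, and the planned ICCs would show poor agreement in such an arm.

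**Conclusion.** The point holds in this limited form: for accuracy, the named procedure and the Aim 2 hypothesis address different contrasts. This follows from setting the sentences side by side and depends on no assumed number.

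The size of the consequence does depend on assumptions: the margin, the discrepancy SD, the bias, equal allocation, and reading the results by condition. Under the ranges used, verdicts for equally accurate arms disagree in 2% to 50% of trials. A reduction in over-reporting from 1.2 to 0.7 SD is never signaled, against about 85% detection by a direct test. The analysis of technique use, which has an explicit Condition term, is not affected.

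**What to change.** Replace the accuracy sentence with a between-condition analysis.

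1. **Outcome:** therapist minus observer ITT-ABP score on the same coded sessions, averaged per client so that it fits the planned data structure.
2. **Model:** the mixed model already planned, with Site and Therapist as random effects. Test the Condition coefficient in the Implementation phase and report the between-condition difference with its confidence interval.
3. **Baseline:** adjust for each therapist's mean Baseline discrepancy where available. This has to be at therapist level, since clients seen in the Implementation phase need not have been treated at Baseline.
4. **Secondary:** repeat with the absolute discrepancy, stated as a different estimand.
5. **Equivalence intervals:** keep them by condition as description of how close each arm comes to the observers, not as the comparison.

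The data are already to be collected. The cost is one or two further models and a Baseline covariate that may be missing for the replacement therapists (two per site are foreseen), so the plan should say how those therapists are handled.

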### Power analysis

Power to detect an experimental effect is based on *n* = 288 audiotaped sessions coded. The study is optimally powered (exceeding .80) to detect a between-condition effect size of *d* = .30 (small) or greater when data are combined across sites. Power calculations were conducted using Optimal Design 3.01 [40]. With nested designs, power is substantially affected by number of sites as well as clusters (therapists and clients) within site [41], and less so by cases (sessions) within cluster. Aggregating across site, and assuming 32 therapists (*unit of randomization*) treating 6 clients each and submitting 1.5 taped sessions for review (*unit of analysis*) and moderately sized within-cluster intraclass correlation coefficients (ICCs) (*ρ* = .05) [42], yields optimal levels of power (exceeding .80) for even small effects (*d* = .30) and increasing power (exceeding .90) with effect sizes of *d* = .40 and greater. Previous research has yielded effect sizes *d* = .40–.50 using a similar design [43].

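### The printed power (above .80 at d = .30, above .90 at d = .40) comes without an alpha and is not the power of the adjusted-alpha Condition tests; on the stated inputs it falls short even at two-sided .05

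*Protocol article*

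**What the plan says.** Two adjacent sections of the protocol article bear on this.

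- **Power analysis.** The basis is given as "Power to detect an experimental effect is based on *n* = 288 audiotaped sessions coded". The inputs are 32 therapists as the unit of randomization, "treating 6 clients each and submitting 1.5 taped sessions for review", and "intraclass correlation coefficients (ICCs) (*ρ* = .05". The result is "The study is optimally powered (exceeding .80) to detect a between-condition effect size of *d* = .30 (small) or greater when data are combined across sites", repeated as "yields optimal levels of power (exceeding .80) for even small effects", with power above .90 from d = .40. The section gives no alpha, no sidedness and no multiplicity allowance. It adds that earlier work with a similar design found d = .40 to .50.
- **Data analysis plan.** Technique use is analysed in a series of mixed models with a dummy-coded Condition variable at therapist level, and "alpha will be adjusted to account for multiple contrasts". The number of contrasts, the family and the method are not given.

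Nothing in the article links the power figures to the adjusted alpha.

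**The concern.** Power belongs to a particular test at a particular threshold. The Data analysis plan makes the threshold for the Condition contrasts on technique use stricter than the nominal level. The Power analysis shows no sign of allowing for this. If the printed figures belong to a looser threshold, they describe a test that will not be run.

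The Power analysis is the article's only justification of sample size, and the Condition contrast is the randomized comparison of Aim 2. If the real power is well below the printed power, a non-significant adjusted contrast is much more likely than the article implies. It could then be misread as showing that feedback plus consultation adds nothing to training alone.

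**Working it through.** **Inputs from the Power analysis:** 32 therapists; 6 × 1.5 = 9 sessions each; 32 × 9 = 288 sessions; ρ = .05; d = .30 and .40.

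**Assumptions, not printed:** 16 therapists per arm; two-sided tests; Bonferroni with k = 2, 3 or 4 contrasts (k = 2 would fit one contrast each for the FT and CBT scales).

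**Step 1. Try to reproduce the printed figures at two-sided .05.**

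- Design effect = 1 + (9 − 1) × .05 = 1.40
- Effective sessions = 288 / 1.40 = 205.7
- SE(d) = 2 / √205.7 = .139
- Noncentrality = d / SE = 2.15 at d = .30 and 2.87 at d = .40
- Noncentral t with 32 − 2 = 30 df: power **.549** at d = .30 and **.793** at d = .40

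The printed .80 and .90 are not reached. Variants:

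| Variant | d = .30 | d = .40 |
|---|---|---|
| Normal approximation, design effect 1.40, two-sided .05 | .576 | .818 |
| Blocking on 4 sites that removes all between-therapist variance (27 df), two-sided .05 | .712 | .919 |
| No clustering at all (normal approximation), two-sided .05 | .721 | .924 |
| One-sided .05, clustering kept (30 df) | .676 | .877 |
| One-sided .05, clients as the only clusters | .808 | .956 |
| One-sided .05, no clustering | .816 | .960 |

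Of the variants tried, only one-sided .05 with therapist clustering ignored takes d = .30 above .80.

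**Step 2. Find the alpha the printed figures would need.** With the Step 1 model (30 df), power of .80 at d = .30 needs a two-sided alpha of about .20, and .90 at d = .40 needs about .13. Both are looser than .05. An adjustment for multiple contrasts moves the other way.

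**Step 3. Power under the written rule, on the article's inputs (30 df).**

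| Contrasts k | alpha = .05/k | d = .30 | d = .40 | d detectable with .80 power |
|---|---|---|---|---|
| 1 | .05 | .549 | .793 | .404 |
| 2 | .025 | .429 | .694 | .449 |
| 3 | .0167 | .365 | .632 | .474 |
| 4 | .0125 | .324 | .588 | .491 |

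**Step 4. Isolate the cost of the adjustment.** Suppose the printed .80 and .90 were correct at two-sided .05. Take the noncentrality that gives each figure and re-test at .05/k. Under the normal approximation the noncentrality for .80 is .842 + 1.960 = 2.802, and for .90 it is 1.282 + 1.960 = 3.242.

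| k | From .80, normal | From .80, 30 df | From .90, normal | From .90, 30 df |
|---|---|---|---|---|
| 2 | .712 (−8.8 points) | .703 (−9.7) | .841 (−5.9) | .833 (−6.7) |
| 3 | .658 (−14.2) | .642 (−15.8) | .802 (−9.8) | .787 (−11.3) |
| 4 | .619 (−18.1) | .597 (−20.3) | .772 (−12.8) | .751 (−14.9) |

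Rounded, the loss is 6 to 10 points for two contrasts, 10 to 16 for three and 13 to 20 for four.

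**The case against.** The best defence has three parts.

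- **The two sections may concern different things.** The Power analysis refers to a single between-condition effect, and the Data analysis plan singles out one contrast of chief interest just before the adjustment clause. The power might be meant for that one contrast at full alpha, with the adjustment covering the rest. The article states no alpha for the power figures, so saying that they used an unadjusted .05 is an inference. This stands as a point about intent. It does not rescue the numbers, because the stated inputs do not give .80 at d = .30 or .90 at d = .40 even at unadjusted two-sided .05.
- **The size of the loss rests on unprinted choices.** The number of contrasts and the method could reasonably be left to an analysis plan that is not shown, and a method less conservative than Bonferroni would generally cost less. This stands. A reader might infer that the adjustment must cost at least 10 points of power. The article does not support that as a floor: with two Bonferroni contrasts the loss is 8.8 to 9.7 points from .80 and 5.9 to 6.7 points from .90.
- **Most of the shortfall comes from elsewhere.** At d = .30 the gap from .80 to .549 is about 25 points before any adjustment, and two contrasts take off a further 12 (.549 to .429). This is correct, so the two components are kept apart in the working. It does not remove the point: repairing only the calculation at .05 would still give the power of a different test from the one planned.

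**Conclusion.** The point holds in a bounded form. The printed power is not a property of the written decision rule. On the article's inputs, power is about .55 at d = .30 and .79 at d = .40 at two-sided .05, before any adjustment. The adjustment lowers it to about .43 and .69 with two contrasts, .37 and .63 with three, and .32 and .59 with four. At d = .40, the lower end of the range the article cites from earlier work, two adjusted contrasts give about .69 where the article claims above .90.

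The direction is certain: any tightening of alpha reduces power. The amount depends on equal allocation, two-sided testing, Bonferroni and the assumed number of contrasts, none of which is printed. The statement should be corrected, but the design itself is not invalidated.

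**What to change.** In the Power analysis, do one of the following.

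1. State the alpha, its sidedness and the number of Condition contrasts that share it, then restate power and detectable d at the adjusted level. With two contrasts at .025 this would read about .43 at d = .30, .69 at d = .40, and a detectable d of about .45.
2. Name one Condition contrast on technique use as primary at two-sided .05 and apply the adjustment in the Data analysis plan to the remaining contrasts only. Restate the primary contrast's power: about .55 at d = .30, .79 at d = .40, and a detectable d of about .40.

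If the original power calculation used an input that is not printed, such as one-sided testing or variance explained by site, that input should be stated so that the figure can be checked.

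The cost is a recalculation and one or two sentences. No extra therapists or data are needed. The stated power becomes less favourable. The article reports that enrolment had not begun, so the change could be made before any data existed.
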